### Predictors

We will investigate and adjust for the following core predictors: age, sex, comorbidities and socioeconomic deprivation. A description of the definitions for these core predictors, and how they will be assessed, is provided in table 4.

**Table 4 T4:** Definitions for core predictors associated with risk of adverse COVID-19 outcomes

Predictor	Definition
Age	A continuous measure of age (in years) at the index date (1 February 2020), calculated using date of birth as recorded in HR or professional registration databases.
Sex	A categorical measure (female/male/other) as recorded in HR or professional registration databases.
Comorbidities	A categorical measure counting the number of comorbidities for each individual (0, 1 or 2 or more) obtained from primary care records and supplemented with secondary care records in analyses conducted in the hospitalised cohort. Comorbidity count will incorporate conditions from the NHS Digital shielded patient list algorithm and others found to be associated with adverse COVID-19 outcomes.
Socioeconomic deprivation	An ordinal measure using quintiles of the Index of Multiple Deprivation (IMD), the official measure of relative deprivation for small areas in each country, based on residential postcode as recorded in HR or professional registration databases. Where residential postcode is not provided workplace postcode will be used as a surrogate.

HR, human resource; NHS, National Health Service.

Elevated body mass index (BMI), obesity and smoking are also considered key predictors for adverse COVID-19 outcomes;^9 23 24^ however, are likely to be missing for large proportions of the identified cohort. Furthermore, missingness in EHR data is unlikely to be random, preventing standard imputation approaches. Thus, BMI and smoking will not be included as independent predictors in the primary study but instead in a sensitivity analysis exploring COVID-19 outcomes within HCWs where this information is available in primary or secondary care medical records, within 24 months prior to the study start date.

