## Introduction

COVID-19 has been declared a global pandemic. Since the first reported cases in December 2019, over 110.7 million cases and 2.4 million deaths have been reported worldwide.^1^ Consistent evidence identifies advanced age, male sex, socioeconomic deprivation and chronic comorbidities as core predictors for COVID-19 adverse outcomes.^2–5^

The COVID-19 pandemic has disproportionately impacted historically disadvantaged populations.^6^ In the UK, higher infection and mortality rates are observed in areas with greater deprivation^7^ and among ethnic minorities.^8–12^ This has prompted calls to prioritise the publication of data disaggregated by ethnicity and to conduct research which increases our understanding of risk in these populations.^13 14^ Ethnicity is a complex construct which represents social, biological or genetic differences between populations.^15^ Potential explanations for COVID-19-related health disparities between ethnic groups include socioeconomic, cultural, behavioural, biological or pathophysiological differences.^16^ It is recommended that investigations into ethnicity-related health inequality should also consider interrelated factors such as deprivation, religion and pre-existing conditions. This approach serves to highlight the interplay between ethnic disparities and economic inequality^13^ and disentangle the independent importance of these factors.^14^

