### Study population

The cohort will include all adult (aged 16 years and over) HCWs captured by HR records or registered with at least one professional regulator on 1 February 2020, excluding those which linkage to EHRs is unsuccessful. HCWs with missing ethnicity, occupation, age, sex or postcode will be excluded from the main analysis. For the HR substudy, only those actively working will be included, thus excluding those on parental, sickness or disability leave for the duration of study period.

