### Main exposures

The main exposure of interest is ethnicity, which is likely to be inconsistently recorded across databases. We will primarily assign ethnicity using staff HR records (ESR or SWISS) and registration databases (if not included/missing from HR records). If ethnicity is missing from these databases, linked EHRs will be assessed. Those with ethnicity recorded as ‘not stated’ or with completely missing ethnicity information will be excluded from the main analyses. Ethnicity will be categorised based on ONS groupings (table 2).

**Table 2 T2:** ONS ethnicity groupings

Broad ethnic categories	Ethnic groups
White	English/Welsh/Scottish/Northern Irish/British Irish Gypsy or Irish Traveller Any other White background
Mixed/multiple ethnic groups	White and Black Caribbean White and Black African White and Asian Any other mixed/multiple ethnic background
Asian/Asian British	Indian Pakistani Bangladeshi Chinese Any other Asian background
Black/African/Caribbean/Black British	African Caribbean Any other Black/African/Caribbean background
Other ethnic group	Arab Any other ethnic group

ONS, Office for National Statistics.

A more granular analysis will incorporate subdivisions of ethnicity (particularly within Asian/Asian British category) if a sufficient number of events are observed.

Occupational group (and its interaction with ethnicity) is also of primary interest. We will assign occupation for the main cohort using data recorded on 1 February 2020 from either HR records or data held by the regulating bodies and the following categories informed by version 17.1 of the NHS Occupational Code Manual (*NHS Digital*):

Ambulance staffAdministrations and estates staffHealthcare assistants and other support staffMedical staffDental staffNursing, midwifery and health visiting staffNursing, midwifery and health visiting learnersScientific, therapeutic and technical staffHealthcare sciencesGeneral payments

A more granular analysis will incorporate subdivisions of occupational groups (particularly the Medical staff group) if a sufficient number of events are observed.

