### Sample size

Sample size will be driven by the number of HCWs captured by the registration databases, with complete exposure information and successful linkage to healthcare data. The analysis plan is informed by likely event rates for each outcome, undertaking more sophisticated analyses for outcomes with sufficient power to provide meaningful results.

We will consider our largest primary data source (ESR) which captures 1.4 million NHS employees in England and Wales, for a conservative estimate of potential precision. The COVID-19 Infection Survey estimate 6.2% (95% CI: 5.0% to 7.6%) of adults in England would be seropositive for anti-SARS-CoV-2 antibodies.^27^ Broadly assuming an equal infection rate in Wales, and that HCWs captured by the ESR represent the general population with a similar infection rate, we could expect to capture approximately 86 600 HCWs with history of COVID-19. A large proportion of the infected population will be asymptomatic, and a recent US study projected that 63% of infected cases went undiagnosed.^28^ Assuming a similar diagnosis rate in England and Wales, we could expect to identify 32 042 COVID-19 cases. Of adults diagnosed with SARS-CoV-2 infections, the estimated hospitalisation rate is 25%^29^ and mortality rate is 6.4%.^28^ We could therefore expect to observe a minimum of 8000 hospitalisations and 2050 deaths resulting from COVID-19.

NHS workforce statistics data show 79.2% of the NHS workforce is White, 10.0% Asian and 6.1% Black. If associations between ethnicity and COVID-19 outcomes represent those observed in the general population, we could report differences between COVID-19 infection for Asian and Black ethnic categories compared with White with 0.1% and 0.2% precision, respectively. Similarly, in those with confirmed SARS-CoV-2 infection, we could report differences in COVID-19 mortality between Asian and Black ethnic categories, compared with White, with 0.9% and 0.8% precision respectively.

We will supplement the ESR with other HR databases and professional registration data sets, including SWISS, with an additional 170 000 HCWs in Scotland and the GMC, with an additional 336 000 GPs not captured by ESR. This increases the total number of HCWs incorporated into our analyses and should ensure sufficient numbers of outcome events.

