### Associations between ethnicity, occupation and COVID-19 outcomes

The relationship between ethnicity and COVID-19 outcomes will be assessed using Poisson, logistic and flexible parametric time-to-event regression models (table 3: COVID-19 outcomes and definitions, identified via listed data sources, to be asessed in UK HCW cohort and within listed subgroups, via listed analysis approach in the planned study). For each outcome, multivariable models will incorporate ethnic category and occupational group, and their interactions, adjusted for the four core predictors. The analyses will be conducted by country, and country-specific results combined using meta-analysis methods to produce UK estimates. We will report incidence rate ratios, ORs or HRs with 95% CIs and p-values. Forest plots and cumulative incidence curves will be produced. Interactions between ethnicity and other predictors will be presented graphically to aid interpretation. Model assumptions will be assessed.

We will use directed acyclic graphs to map hypothesised causal associations between ethnicity, occupational group, the core predictors and COVID-19 outcomes. Mediation analysis methods will then be applied to disentangle the direct, indirect and mediated interactive effects of ethnic category and COVID-19 outcomes. The direct effects estimated using the approach are likely to be related to unmeasured explanatory factors, including experiences of structural discrimination and racism, rather than any genetic predispositions for differing outcomes.

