### Sensitivity and additional analyses

Dependent on the number of HCWs and events captured, we intend to conduct the following additional analyses:

*Incorporating BMI and smoking into broad analysis*: adjust for BMI and smoking in COVID-19 outcome models if recorded by EHRs either during, or in the 24 months prior to, the study period.
*Incorporating grouping by organisation*: incorporate clustering of HCWs within organisations by fitting hierarchical models to account for within organisation correlation and between organisation heterogeneity.
*Granular analysis within the ‘Asian/Asian British’* ethnicity category: investigate differences in COVID-19 outcomes between HCWs with South Asian (Indian, Pakistani and Bangladeshi), East Asian (Chinese) and Other Asian backgrounds.Granular analysis within the “medical staff” occupational group: investigate differences in COVID-19 outcomes between medical and dental subcategories.Subgroup analysis within hospital workers: investigate COVID-19 outcomes in hospital workers and cluster HCWs within hospitals using hierarchical models.
*Subgroup analysis of ancillary workers*: investigate COVID-19 outcomes in ancillary workers through trusts that employ them directly.
*Missing ethnicity*: explore approaches to deal with missing ethnicity information.
*Missing data*: use multiple imputation to assess the robustness of our findings to missing data.

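### Where residential postcode is missing, Table 4 substitutes the deprivation quintile of the workplace, which mixes two variables in one core adjuster and under-adjusts the ethnicity estimates for the workers affected

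*Protocol article*

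**What the plan says.** Table 4 (Predictors) defines socioeconomic deprivation as quintiles of the Index of Multiple Deprivation, "based on residential postcode as recorded in HR or professional registration databases". It then gives a fallback: "Where residential postcode is not provided workplace postcode will be used as a surrogate".

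Under Associations between ethnicity, occupation and COVID-19 outcomes, "multivariable models will incorporate ethnic category and occupational group, and their interactions, adjusted for the four core predictors". Deprivation is one of those four. Under Outcome incidence, it is also used to standardise all incidence rates.

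Three other statements bear on the rule:

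- Study population: "HCWs with missing ethnicity, occupation, age, sex or postcode will be excluded from the main analysis". The type of postcode is not specified.
- Main exposures, on ethnicity not found in the HR and registration databases: "If ethnicity is missing from these databases, linked EHRs will be assessed". No such step is stated for postcode.
- Sensitivity and additional analyses: the plan will "use multiple imputation to assess the robustness of our findings to missing data".

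**The concern.** The index describes the area a postcode falls in. A residential postcode gives the worker's home area, and a workplace postcode gives the employer's site. All workers who receive the surrogate at one site share one quintile, whatever their own home area. The covariate then means home deprivation for some workers and site deprivation for others, under a single set of coefficients. Site deprivation may also carry local infection pressure, which is a different construct.

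The Introduction itself reports that "higher infection and mortality rates are observed in areas with greater deprivation", and it names separating ethnicity from deprivation as a reason for the work. If minority staff live in more deprived areas on average, weaker adjustment moves the ethnicity ratio towards its unadjusted value. That is the direction of the study's own hypothesis, and a large sample does not reduce it. In the planned mediation analysis, the same error could move part of a socioeconomic pathway into the direct effect.

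**Working it through.** **What the plan gives.** No figure in the article concerns this rule, so there is no stated number to reproduce. The share of workers without a residential postcode, the deprivation gradient and the home-area distributions are all absent. What follows illustrates direction and order of size.

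**Inputs**

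- Workforce split, from Sample size: "79.2% of the NHS workforce is White, 10.0% Asian and 6.1% Black". White is 79.2%, and all others are 100 − 79.2 = 20.8%.
- Assumed home quintiles, most to least deprived: White 17, 19, 20, 21.5, 22.5%; minority 30, 25, 19, 15, 11%.
- Assumed most-to-least deprived rate ratio g = 1.5 or 2.0, in equal steps on the log scale. For g = 2.0 the relative rates are 2.000, 1.682, 1.414, 1.189, 1.000.
- Assumed true ethnicity ratio 1.30, the same in every quintile.
- Assumed share m on the surrogate, with workplace quintile unrelated to home and spread evenly (20% each).

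**Formula.** For a group with home share D(a), relative rate r(a) and mean rate R = Σ D(a)r(a):

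- share recorded in quintile a: n(a) = (1 − m)D(a) + 0.2m
- mean rate there: [(1 − m)D(a)r(a) + 0.2mR] / n(a)

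The ethnicity ratio is then pooled over recorded quintiles by Mantel-Haenszel.

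**Example, g = 2.0, m = 30%, most deprived recorded quintile.** R is 1.4231 for White and 1.5775 for minority staff.

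- White: n = 0.7 × 0.17 + 0.06 = 0.179; rate = (0.7 × 0.17 × 2 + 0.06 × 1.4231) / 0.179 = 1.807.
- Minority: n = 0.7 × 0.30 + 0.06 = 0.270; rate = (0.7 × 0.30 × 2 + 0.06 × 1.5775) / 0.270 = 1.906.
- Ratio: 1.30 × 1.906 / 1.807 = 1.37.

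The other four quintiles give 1.34, 1.34, 1.38 and 1.46. The pooled value is 1.370.

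**Results**

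| Share on surrogate | g = 1.5 | g = 2.0 |
|---|---|---|
| 0% | 1.3000 | 1.3000 |
| 10% | 1.3154 | 1.3258 |
| 30% | 1.3416 | 1.3702 |
| 50% | 1.3614 | 1.4045 |
| 100% (same as no adjustment) | 1.3822 | 1.4411 |

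At 50% and g = 2.0 the value is 1.40 with the workforce split above, and 1.41 (1.4058) if the two groups are of equal size.

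**Share of confounding left in.** At g = 2.0 and m = 30%: (1.3702 − 1.30) / (1.4411 − 1.30) = 0.50. The same calculation gives 0.18 at 10% and 0.74 at 50%. The loss exceeds m because home and site values share the same strata.

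**If workplace tracks home.** Suppose the workplace quintile equals the home quintile for 40% of surrogate workers beyond chance. The effective share is then 0.6m. Thus 50% behaves like 30% in the table (1.34 to 1.37), and 10% behaves like 6% (1.31 to 1.32).

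**Check with a true ratio of 1.00.** A Poisson model with ethnicity and recorded quintile, at g = 2.0 and workplace unrelated to home, gives 1.02, 1.05 and 1.08 at 10%, 30% and 50%, and 1.11 at 100%.

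**Does a planned analysis catch it?** Multiple imputation acts on missing values, and a filled quintile is not missing. Pay grade enters only the occupation model of the HR substudy. The article states no flag for surrogate values and no analysis restricted to residential postcodes, and the Discussion does not list the surrogate as a limitation.

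**The case against.** The best defence is that the rule may touch few workers. At 10% surrogate use the illustrated ratio moves by about 1 to 2%. The illustration leaves out occupational group, age, sex and comorbidity, all of which the models adjust for. Occupational group already separates medical staff from estates and support staff, so only deprivation differences within occupational groups are at issue. All this stands, and it limits the size. It does not make a site's quintile a measure of home area.

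A reader might also infer four stronger things that the article does not support:

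- **That everyone at a site gets one quintile.** Only workers without a residential postcode are affected; the others keep their own.
- **That Table 4 contradicts Study population.** If postcode there means either kind, a worker with only a workplace postcode stays in. If it means residential, the surrogate never enters the main analysis. The text is ambiguous.
- **That surrogate use follows the source register, and so occupation.** No section says which source lacks home postcodes. The article says regulator registries hold less on workplace location, so the surrogate may not be available there at all.
- **That deprivation is named as the main explanation of ethnic differences.** The Introduction lists socioeconomic differences among several potential explanations and does not rank them.

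Two cautions about the remedy also stand. Data linkage does not say that the returned health files include area of residence. Imputation has its own assumptions: the article doubts standard imputation for BMI and smoking because missingness in health records is unlikely to be random. A condensed article may leave sensitivity checks to a fuller plan, but the substitution is a stated rule and can be judged as written.

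**Conclusion.** The point holds for workers without a residential postcode. For them, Table 4 replaces the intended variable with a different one in a core adjuster, and nothing stated in the plan would reveal or correct it. Under the assumptions shown, a true ratio of 1.30 becomes about 1.32 to 1.33 at 10% surrogate use, 1.34 to 1.37 at 30%, and 1.36 to 1.41 at 50%. The shift is smaller if workplace and home deprivation correlate.

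The direction rests on minority staff living in more deprived areas on average, which is an assumption. The size rests on a share that the article does not give. If very few workers lack a residential postcode, the effect is negligible. The change is worth making because it is cheap and the affected share can be counted once the data are linked.

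**What to change.** 1. Before using the surrogate, take residential area from the linked health records where the providers return it. Main exposures already uses this order of sources for ethnicity.
2. Flag every remaining surrogate value, and report the share by source database, ethnicity and occupational group.
3. Repeat the main models with residential deprivation only. Set surrogate values to missing, once as a complete-case analysis and once within the planned multiple imputation.
4. State in Study population which missing postcode leads to exclusion, so that it agrees with Table 4.

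The cost is one extra derivation, which depends on what the providers return, one sensitivity analysis, and fewer complete cases in that analysis.

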### HR sub-study

This sub-study will consider only those undertaking active employment in the NHS during the study observation period and will be conducted only in regions where data are available.

Additional ethnicity-related predictors include religious belief, nationality, immigration status and country of birth. Additional occupation predictors include primary area of work, role description, full/part time, patient/non-patient facing,^18^ time in current role, organisation type, salary grade, length of service and seniority. Additional exposure-related predictors include absence information and total hours worked. Changes in these predictors will be captured throughout the study period. Time varying covariates will be incorporated to enable the assessment of the impact of changes in COVID-19 exposure over time.

### Patient and public involvement

We have been working with organisations that regulate and represent ethnic minority HCWs, including the GMC, NMC, Royal Colleges and professional associations such as the British Association of Physicians of Indian Origin. They were involved in identifying research questions and deciding study methodology, and are included as members of the study delivery team or collaborators. These organisations are part of the stakeholder group, meeting monthly to monitor study progress and outputs, provide advice on study delivery and disseminate research findings. Representatives from ethnic minority healthcare professionals, including those who have contracted COVID-19, will also input into this stakeholder group. A Professional Expert Panel of doctors, nurses and ancillary staff from varying ethnic backgrounds and genders will meet bimonthly to provide advice and lived experience related to certain aspects of the project.

## Statistical analysis plan

### Statistical principles

Reporting will be in line with Strengthening The Reporting of OBservational studies in Epidemiology (STROBE)^25^ and REporting of studies Conducted using Observational Routinely collected health Data^26^ guidelines. Any dissemination of study findings will follow best-practice guidelines for deductive disclosure. Only aggregate data will be included in publications, 95% CIs will be reported throughout and p-values<0.05 will indicate statistical significance. Multiple testing adjustments will not be made but emphasis will be on effect size rather than statistical significance. Deviations to this protocol and analysis plan will be outlined with justification in the final reporting of the results.

### Sample size

Sample size will be driven by the number of HCWs captured by the registration databases, with complete exposure information and successful linkage to healthcare data. The analysis plan is informed by likely event rates for each outcome, undertaking more sophisticated analyses for outcomes with sufficient power to provide meaningful results.

We will consider our largest primary data source (ESR) which captures 1.4 million NHS employees in England and Wales, for a conservative estimate of potential precision. The COVID-19 Infection Survey estimate 6.2% (95% CI: 5.0% to 7.6%) of adults in England would be seropositive for anti-SARS-CoV-2 antibodies.^27^ Broadly assuming an equal infection rate in Wales, and that HCWs captured by the ESR represent the general population with a similar infection rate, we could expect to capture approximately 86 600 HCWs with history of COVID-19. A large proportion of the infected population will be asymptomatic, and a recent US study projected that 63% of infected cases went undiagnosed.^28^ Assuming a similar diagnosis rate in England and Wales, we could expect to identify 32 042 COVID-19 cases. Of adults diagnosed with SARS-CoV-2 infections, the estimated hospitalisation rate is 25%^29^ and mortality rate is 6.4%.^28^ We could therefore expect to observe a minimum of 8000 hospitalisations and 2050 deaths resulting from COVID-19.

NHS workforce statistics data show 79.2% of the NHS workforce is White, 10.0% Asian and 6.1% Black. If associations between ethnicity and COVID-19 outcomes represent those observed in the general population, we could report differences between COVID-19 infection for Asian and Black ethnic categories compared with White with 0.1% and 0.2% precision, respectively. Similarly, in those with confirmed SARS-CoV-2 infection, we could report differences in COVID-19 mortality between Asian and Black ethnic categories, compared with White, with 0.9% and 0.8% precision respectively.

We will supplement the ESR with other HR databases and professional registration data sets, including SWISS, with an additional 170 000 HCWs in Scotland and the GMC, with an additional 336 000 GPs not captured by ESR. This increases the total number of HCWs incorporated into our analyses and should ensure sufficient numbers of outcome events.

